#### Explorative outcomes

In our trial we have chosen a number of exploratory outcomes, which are not based on power calculations. These include the severity of BPD symptoms, suicide intention and ideation, depression, hopelessness, self-esteem, impulsivity, and anger. We will also examine between-group differences in ‘dosage’ and durations of the respective treatments.

#### Borderline personality disorder symptoms

The severity of features regarding borderline personality symptoms is measured by the Zanarinis Rating Scale for BPD. It is a nine-item, five-point scale (0 to 4, 0 = no symptoms and 4 = severe symptoms) validated, clinician-based diagnostic interview (DSM-IV)
[30]. The categories of symptoms are affective, cognitive, impulsivity, and interpersonal symptoms.

#### Suicide intention and ideation

Suicide intention is measured by Beck’s Suicide Intent Scale (SIS)
[31,32]. It consists of 20 items, where the different circumstances and practical preparations are investigated.

The Beck Suicide Ideation Scale (BSS) is a 19-item self-report questionnaire measuring suicidal thinking
[32]. Items are scored on a Likert scale ranging from 0 to 2, with a higher score indicating more severe suicidal ideation.

#### Depression

Depressive symptoms will be assessed by Hamilton Depression Rating Scale (HDRS) 17-items
[33]. The patients are also subjects to Beck’s Depression Inventory (BDI)
[34,35], a 21-item self-report inventory of the depressive symptomatology measuring depression. The BDI is the most widely used research instruments and the items are rated on a Likert scale from 0 to 3, where higher scores indicate a more severe level of depressive symptoms.

#### Hopelessness, self-esteem, impulsivity, anger

The Becks Hopelessness Scale (BHS) consists of 20 true-false items pertaining to future outlook
[36]. Rosenberg’s Self- Esteem scale (RSE) is used to assess the self-esteem. It consists of 10 items and is a Likert scale with answers using a four-point scale -from strongly agree to strongly disagree
[37].

Barratts Impulsivity Scale 11 (BIS-11) is a 30-item questionnaire measuring impulsive personality traits
[38]. It yields a total score, three second-order factors, and six first-order factors
[39]. To measure anger, we will use State Trait Anger Scale (STAS), developed by Charles Spielberger
[40]. It consists of 20 items in a self-report questionnaire and is rated on a Likert scale with answers using a four-point scale -from never to always.

### Sample size and statistical analyses

Based on previous estimations, we expect the risk of renewed self-harming acts within their first year to be 50 percent in the CAMS treatment group
[6]. We expect the DBT to be able to reduce this risk to 25 percent, a relative risk reduction of 50%. With a power of 90% and a type one error probability associated with this test of 0.05, we plan to randomize 154 patients, with about 77 patients in each intervention group. We will handle missing data using logistic regression with multiple imputations as described below.

The two group baseline characteristics will be compared using Student’s *t*-test for independent samples or a chi-square test for binary variables.

The primary analysis will be based on the intention-to-treat principle; that is, data from all patients will be included in the treatment group to which they were allocated regardless of degree of compliance.

Binary outcomes will be analyzed using logistic regression and continuous outcomes will be analyzed using linear regression with baseline variables as sex and previous deliberate self-harm as a covariates.

If more than 5% of the primary outcome is missing at follow-up, we will use multiple imputations (SPSS version 19.0). If this is the case, the multiple imputations will be considered the primary result. For multiple imputations, we will use a linear regression model with 100 imputations and 20 iterations. The pooled estimates from the imputations will subsequently be used for our analysis.

We will use two-tailed tests for statistical significance with alpha set at *P* <0.05.

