## Methods/Design

Our plan is to compare 16 weeks treatment of DBT versus CAMS. The primary outcome will be the ratio of participants with suicide attempts or non-suicidal deliberate self-harming acts (self-reported and registered in medical records) during the treatment period in the treatment period and at follow-up until week 28 after randomization.This trial is designed as a single-center, two-armed, parallel-group, observer-blinded randomized clinical superiority trial (Figure 
1).

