### Outcomes

#### Primary outcome

The primary outcome will be measured as the ratio of deliberate self-harm before and after treatment (week 0 compared with week 28). The Suicide attempt and Self-Injury Interview (SASII)
[28] will be used to collect these data and direct questions in the follow-up interview regarding self-harming behavior after inclusion in the trial. We will also obtain information concerning numbers of deliberate self-harm and suicide attempts through medical records.

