## Discussion

The DiaS trial is designed as a pragmatic trial, with the intention of intervening in the exiting clinical outpatient setting, so one could argue the patient population is selected beforehand. The Excellence Centre for Suicide Prevention has their exclusion criteria before offering treatment as mentioned before and can exclude patients for whom treatment can appear too demanding. The chosen target group includes patients with emotional dysregulation leading to suicide attempts. This patient group is over-represented in the Centre of Excellence in Suicide Prevention. The chosen experimental DBT treatment is based on a modified DBT manual but where all the skills taught are maintained. The DBT treatment period of 16 weeks is shorter than in the majority of other randomized clinical trials performed
[16]. The considerations of these modulations are the excepted occurrence of the lesser chronicity and severity in BPD symptoms in the target group of patients. The patients only have to fulfill two out of nine BPD criteria according to the DSM-IV. Regarding the CAMS-informed supportive psychotherapy given to the control group, this treatment has been an obvious choice as the majority of therapist in the Excellence Centre for Suicide Prevention use this treatment. This treatment group can be considered as an optimized ‘treatment-as-usual’ control group, where the therapists are trained and supervised, and treatment adherence is rated.

The two different intervention groups will receive different amounts of time of individual psychotherapy, and the CAMS group is not offered skill training in groups. We consider the different amounts of time in the two groups as inevitable because of the different basic construction of the two psychotherapeutic treatments. In the CAMS- intervention group the therapist has to finish the treatment when achieving three consecutive non-suicidal scores on the SSF. A strength of this trial is the centralized randomization
[42], which reduces the risk of selection bias. We will perform blinded outcome assessment to reduce bias
[43]. We will use intention-to-treat analysis and multiple imputations to reduce the bias introduced by missing data in our analysis
[43].

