A related post-hoc consideration is the potential ‘cost-effectiveness’ of the respective treatments in relation to frequencies of hospitalizations, emergency department visits, and primary care visits. The cost-effectiveness of clinical care for high-risk patients was previously examined in a retrospective study of CAMS versus treatment-as-usual with suicidal outpatients
[44] and is a topic of increasing importance within contemporary mental health care around the world.

The DiaS trial is a single center trial and can therefore be considered as a pilot trial for multicenter trials in the future. In order to obtain external validity, we need multicenter trials. The DiaS trial has a 52-week follow-up period to investigate deliberate self-harm and suicide attempts after treatment. This knowledge can be useful in the design of trials, in regard to treatment duration or to booster treatment sessions. Moreover we need trials showing comparable effects both during the intervention period and the post-intervention period.

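### The 90% power rests on first-year self-harm risks, but the primary outcome is read at week 28, so that power is not supported for the primary endpoint

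*Protocol article*

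**What the plan says.** In the protocol article, Sample size and statistical analyses, the planning risk in the control arm is tied to a year: "we expect the risk of renewed self-harming acts within their first year to be 50 percent in the CAMS treatment group". The treatment effect refers to that same quantity: "We expect the DBT to be able to reduce this risk to 25 percent, a relative risk reduction of 50" per cent. The size follows: "With a power of 90% and a type one error probability associated with this test of 0.05, we plan to randomize 154 patients", about 77 per arm. Testing is two-sided: "We will use two-tailed tests for statistical significance with alpha set at" 0.05.

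The primary outcome has a shorter horizon. Methods/Design counts participants with a suicide attempt or self-harming act during treatment and "at follow-up until week 28 after randomization". The Primary outcome section compares before and after treatment, "week 0 compared with week 28". The Abstract also names week 28.

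A week-52 interview is scheduled, and the Discussion gives its purpose: "The DiaS trial has a 52-week follow-up period to investigate deliberate self-harm and suicide attempts after treatment". It is nowhere called primary.

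**The concern.** A sample-size calculation supports a power claim only if its risks refer to the endpoint that will be tested. Here the risks cover 52 weeks and the endpoint covers 28. No section gives a week-28 risk or says that the first-year risks are expected to have been reached by then. This is not a detail that could be left to an analysis plan, because the article states both the planning risk and the endpoint and their time windows differ.

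At stake is how a neutral result would be read. A reader who takes the 90% at face value would treat a neutral week-28 result as stronger evidence against the planned effect than the design may justify. The Discussion also presents the trial as a pilot for later multicentre trials, so the planning basis could be carried forward.

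**Working it through.** **Inputs from the protocol article:** first-year risk 50% (CAMS) and 25% (DBT); two-sided alpha 0.05; power 90%; 77 per arm; primary outcome at week 28. **Not given, so assumed below:** the week-28 risk in either arm.

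**Step 1. Reproduce the stated size.** Pooled two-proportion formula without continuity correction, with p̄ = (p1 + p2)/2:

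n = [1.960·√(2p̄(1 − p̄)) + 1.282·√(p1(1 − p1) + p2(1 − p2))]² / (p1 − p2)²

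With p1 = 0.50, p2 = 0.25 and p̄ = 0.375: n = (1.342 + 0.848)² / 0.0625 = 76.7, so 77 per arm and 154 in total. This matches the article. Power at 77 per arm is 90.1%, so the size has no spare margin.

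**Step 2. What is certain at week 28.** The cumulative risk of a first renewed act by week 28 is at most 50% with CAMS and at most 25% with DBT. It equals those values only if nobody has a first event in weeks 29 to 52.

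**Step 3. Power at week 28 under stated assumptions.**

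Power = Φ{[(p1 − p2)·√77 − 1.960·√(2p̄(1 − p̄))] / √(p1(1 − p1) + p2(1 − p2))}

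For constant hazard in each arm, the week-28 risk is 1 − (1 − first-year risk)^(28/52):
- CAMS: 1 − 0.50^0.538 = 31.1%
- DBT: 1 − 0.75^0.538 = 14.4%
- Power = Φ[(1.474 − 1.162)/0.581] = Φ(0.537) = 70%

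| Assumption | Week-28 risks, CAMS v DBT | Power, 77 per arm |
|---|---|---|
| All first-year events by week 28 | 50% v 25% | 90% |
| 95% of them in each arm | 47.5% v 23.75% | 88% |
| 90% of them in each arm | 45% v 22.5% | 85% |
| 80% of them in each arm | 40% v 20% | 78% |
| Constant hazard in each arm | 31.1% v 14.4% | 70% |
| Constant-hazard control risk, relative reduction held at 50% | 31.1% v 15.6% | 63% |

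**Step 4. Sensitivity to how the effect is carried back.** Constant hazard implies a hazard ratio of ln 0.75 / ln 0.50 = 0.415. Holding that ratio instead of a 50% relative reduction gives 86% power at a control risk of 45%, and 82% at 40% (v 19.1%). The Abstract's figure of 160 participants (80 per arm) moves the constant-hazard result only from 70% to 72%.

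**Step 5. What would keep 90% with 154 patients.** Either all first-year events come by week 28, or the early effect is larger than a halving: 40% v 16.8% (a 58% reduction) or 31.1% v 10.3% (a 67% reduction). The article states neither.

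**The case against.** The strongest defence is that the calculation is correct and the loss may be small. Participants enter within a month of a suicide attempt, and the Background cites a review in which most treatment gain comes in the first four months of DBT. Neither fixes the event curve, but neither favours a flat hazard. If 90% of first-year events come early, power is still about 85%; if none come after week 28, nothing is lost. The analysis itself stays valid. All of this stands, and it limits the size of the point. It does not supply the missing week-28 risks.

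Several stronger readings are tempting, and the documents do not support them:

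- **That power is known to be about 70%.** This is the constant-hazard scenario only.
- **That the trial has a 30% chance of missing a halving of risk.** This mixes two effects. The 70% belongs to 31.1% v 14.4%, a 54% reduction. A true halving from 31.1% has 63% power, a 37% chance of a miss.
- **That 50% is too high for this population.** The Discussion mentions "the excepted occurrence of the lesser chronicity and severity in BPD symptoms in the target group of patients", but that concerns symptoms of the personality disorder and explains the shorter DBT course. It says nothing about repeat self-harm after a recent attempt.
- **That power falls further through dropout or simple proration of risk by 28/52.** The article gives no loss rate, and proration implies a hazard that rises over the year, which nothing in it suggests.

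**Conclusion.** The point holds as a mismatch of time horizons, not as an arithmetic error. The 90% power is right for 50% v 25% at one year. It is not supported for the week-28 primary outcome and is probably too high there. "Probably" is as far as the documents go: week-28 risks are bounded above by the first-year risks, but their distance below that bound, and the effect at that time, are not given. Across the assumptions tried, power with 77 per arm runs from 63% to 90%, and the top value needs no first events after week 28 (or an early effect larger than the article states). Even the mild case of 90% of events by week 28 raises the type II error from about 10% to about 15%.

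**What to change.** In Sample size and statistical analyses, state the expected week-28 risks in both arms with their justification, and restate the power of 154 patients for the week-28 endpoint as a range that depends on those assumptions. Alternatively, justify why 50% v 25% is expected to apply at week 28. The scenarios above show the form such a range could take; the risks entered should be the sponsor's own.

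No extra enrolment is asked for. Nor is a move of the primary time point to week 52: recruitment is already under way and three sections fix week 28, so changing it to preserve a power figure would be a debatable trade. The cost is a rewritten paragraph and, most likely, a less favourable stated power.

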### Randomization and blinding

Patients will be randomized into one of two treatment arms. The randomization is stratified by sex and previous number of self-harm acts (one versus multiple). This is done to avoid the risk of patients with multiple self-harm acts being overrepresented in one of the treatment groups. The Copenhagen Trial Unit (CTU) will generate a computer-generated random sequence randomization, using alternating block sizes unknown to the investigators. The trial staff will contact the CTU for information about allocation. The above-mentioned procedure ensures adequate allocation concealment. The patients and therapists will not be blinded. We will use blinded outcome assessors (see outcomes below).

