### Assessments

The patients will be subjected to four almost identical assessments. The first baseline assessment will be performed in continuity with the assessment and validation of the inclusion and exclusion criteria. Also the strata used for the randomization will be obtained in the first interview with the patient. The second assessment will occur after treatment has ended in week 17 after inclusion in the trial. The third and fourth assessment will occur at a follow-up interview after week 28 and week 52 after inclusion.

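### The regressions for the exploratory symptom scales name sex and previous self-harm as covariates but omit the baseline score of the scale, which costs precision without causing bias

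*Protocol article*

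**What the plan says.** Under Sample size and statistical analyses, the protocol article gives one model for all continuous outcomes: "continuous outcomes will be analyzed using linear regression with baseline variables as sex and previous deliberate self-harm as a covariates". The two covariates match the strata under Randomization and blinding: "The randomization is stratified by sex and previous number of self-harm acts (one versus multiple"). No section names the baseline value of a scale as a covariate, and none says whether the dependent variable is the follow-up score or the change from baseline.

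The Assessments section says "The patients will be subjected to four almost identical assessments", placed at baseline and around weeks 17, 28 and 52. On timing it adds: "The first baseline assessment will be performed in continuity with the assessment and validation of the inclusion and exclusion criteria".

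The outcomes concerned are listed under Explorative outcomes: "These include the severity of BPD symptoms, suicide intention and ideation, depression, hopelessness, self-esteem, impulsivity, and anger". The same section gives their status: "we have chosen a number of exploratory outcomes, which are not based on power calculations".

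**The concern.** For a symptom scale measured twice in the same person, the baseline score is usually the best single predictor of the later score. The stated model leaves it out, although the trial can be expected to hold it for nearly every participant before randomisation. Sex and a one-versus-multiple count of self-harm acts are unlikely to stand in for it, and stratifying on them does not directly balance the scale scores.

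Two things are at stake. Confidence intervals for the arm differences on these scales would be wider than the data require. And part of any chance difference in baseline severity between the arms would stay in the follow-up comparison. Since these outcomes were not powered, nothing in the sample size makes up for the lost precision.

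**Working it through.** **The plan's own figure.** The sample size concerns the binary primary outcome: 50% against 25%, 90% power, two-sided 0.05. With pooled variance under the null and no continuity correction, the mean proportion is 0.375 and

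n per arm = [1.960·√(2·0.375·0.625) + 1.282·√(0.50·0.50 + 0.25·0.75)]² / 0.25² = (1.342 + 0.848)² / 0.0625 ≈ 76.7.

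This rounds up to 77 per arm, 154 in total, with power 90.1%. The stated figure reproduces. It does not depend on how the continuous outcomes are modelled.

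**Inputs for the point itself.**
- 77 per arm (Sample size and statistical analyses).
- Covariates: sex and previous self-harm (same section).
- Correlation r between baseline and follow-up score: not given; assumed to be 0.3, 0.5 or 0.7. Strictly, r is the partial correlation given sex and previous self-harm.
- An arm difference of 0.4 SD for the power illustration: assumed.

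**Case A: the follow-up score is analysed.** Adding the baseline score multiplies residual variance by f = 1 − r² and the interval width by √f. The sample that would give the same precision without the covariate is 77/f per arm, rounded up. Power is Φ(0.4/√(2f/77) − 1.960). The difference detectable with 80% power is (1.960 + 0.842)·√(2f/77) SD.

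| r | f | variance cut | interval narrower by | equivalent total N | power at 0.4 SD | detectable at 80% |
|---|---|---|---|---|---|---|
| not adjusted | 1 | – | – | 154 | 70% | 0.45 SD |
| 0.3 | 0.91 | 9% | 4.6% | 170 | 74% | 0.43 SD |
| 0.5 | 0.75 | 25% | 13.4% | 206 | 82% | 0.39 SD |
| 0.7 | 0.51 | 49% | 28.6% | 302 | 94% | 0.32 SD |

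**Case B: the change from baseline is analysed.** With equal variances at both times, a change score has variance 2(1 − r)σ². The baseline-adjusted model has (1 − r²)σ². The ratio is (1 + r)/2, so the cut is (1 − r)/2.

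| r | ratio | variance cut | interval narrower by |
|---|---|---|---|
| 0.3 | 0.65 | 35% | 1 − √0.65 = 19.4% |
| 0.5 | 0.75 | 25% | 1 − √0.75 = 13.4% |
| 0.7 | 0.85 | 15% | 1 − √0.85 = 7.8% |

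The gain rises with r in case A and falls with r in case B. At r = 0.5 the two agree.

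**Chance imbalance.** The standard error of the baseline mean difference is √(2/77) = 0.16 SD, so 95% of randomisations give a difference within ±1.96·0.161 ≈ ±0.32 SD. In case A, about r times the realised difference passes into the follow-up contrast. At the edge of that range this is 0.3·0.316 = 0.09 SD, 0.5·0.316 = 0.16 SD or 0.7·0.316 = 0.22 SD.

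**The case against.** **The list may be open.** The sentence is awkward, and *as* could mean *such as*, which would make the two variables examples. That reading is possible, but it does not put the baseline score into the model. It would leave the choice of covariates undefined, which the same amendment cures.

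**A condensed article leaves model detail elsewhere.** A per-scale covariate could be given in the full protocol or an analysis plan, neither of which is at hand. This would count if the article were silent. It is not: it states a model and its covariates, and a later document that follows the sentence would carry the omission forward.

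**The outcomes are exploratory.** This stands. No confirmatory conclusion rests on these models, which limits the importance of the point.

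**Nothing is invalid.** This stands too. A reader might infer that the planned comparisons are biased, or that baseline imbalance carries over in full. The documents do not support either. Allocation is randomised, so regression on the strata is unbiased over repeated randomisations and ordinary intervals already allow for chance imbalance. When the follow-up score is analysed, only about r times the realised imbalance carries over.

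**The size is assumed.** This stands. A reader might take the r = 0.7 row of case A, where 154 adjusted patients match about 302 unadjusted, as the cost of the omission. That needs a high correlation and analysis of the raw follow-up score, and the article states neither. Against a change score at the same r, the gain is equivalent to 1/0.85 ≈ 1.18 times the patients.

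**Availability of baseline scores is inferred.** The article describes nearly identical assessments but gives no schedule by scale. The inference is reasonable, but the point must be limited to scales in fact measured at both times.

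**Conclusion.** The point holds as a matter of efficiency. The stated model omits a baseline score that the trial can be expected to hold. The consequence is less precision, and more sensitivity to chance imbalance, in the exploratory symptom scales. Treatment dosage and duration have no baseline value and are outside it.

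The size depends on two things the article does not give: the partial correlation and the form of the dependent variable. Over correlations from 0.3 to 0.7, the avoidable residual variance runs from 9% to 49% if follow-up scores are analysed and from 35% to 15% if change scores are. Both forms give 25% at 0.5. The loss is therefore modest to substantial, and the remedy is nearly free. It is worth making, but the trial's main conclusion does not turn on it.

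**What to change.** In Sample size and statistical analyses, split the sentence on binary and continuous outcomes and word the continuous part along these lines: *Each scale measured at baseline and at follow-up will be analysed by linear regression on the follow-up score, with treatment arm, the baseline score of the same scale, sex and previous deliberate self-harm as covariates.* Present the list as complete, and fix it before outcome data are examined.

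This settles three things at once: the missing covariate, whether follow-up or change scores are analysed, and whether the covariate list is open. The cost is one degree of freedom per model, with no further data, visits or patients.

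A linear mixed model over weeks 17, 28 and 52 with the baseline score as covariate would also use participants who miss a visit. That is an optional and separate choice, with its own modelling decisions, and the point does not depend on it.

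### The exploratory scales get a single-visit linear regression without the baseline score, and the only operative imputation rule depends on the primary outcome, so scores already collected may go unused

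*Protocol article*

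**What the plan says.** All statements are in the Protocol article.

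- **Model.** Under Sample size and statistical analyses, "continuous outcomes will be analyzed using linear regression with baseline variables as sex and previous deliberate self-harm as a covariates". No repeated-measures model is named, and the scale's own baseline value is not among the covariates.
- **Imputation rule.** The same section says: "If more than 5% of the primary outcome is missing at follow-up, we will use multiple imputations (SPSS version 19.0". The imputation model follows: "For multiple imputations, we will use a linear regression model with 100 imputations and 20 iterations". No trigger is given for the scales. The sentence on intention to treat in that section speaks of the primary analysis.
- **General sentences.** The sample-size paragraph says "We will handle missing data using logistic regression with multiple imputations as described below". The Discussion says "We will use intention-to-treat analysis and multiple imputations to reduce the bias introduced by missing data in our analysis". Neither is limited to the primary outcome, and neither gives a rule for the scales.
- **Visits.** Under Assessments, "The patients will be subjected to four almost identical assessments", at baseline and week 17, and then: "The third and fourth assessment will occur at a follow-up interview after week 28 and week 52 after inclusion". The timing counts from inclusion and is the same in both arms.
- **Sources.** Under Primary outcome, self-harm is collected by interview and also from medical records. The sections describing the scales name no second source.
- **Status.** Under Explorative outcomes, the scales are exploratory and not powered.

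**The concern.** A linear regression of a week 28 score, without imputation, uses only participants who have that score. Someone seen at baseline and week 17 but not at week 28 is then left out of the week 28 comparison, although two scores strongly related to the missing one are on file.

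The 5% trigger may not help. Because records can supply part of the primary outcome, its missingness can stay under 5% while many more participants lack a depression, ideation or hopelessness score. The rule is tied to the outcome likely to be the most complete.

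Two things are at stake: precision on every scale, and protection against bias if those who stop attending differ between arms in their earlier scores.

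**Working it through.** **1. The plan's own figure.** The article gives 50% against 25%, 90% power, two-sided alpha 0.05 and 77 per arm.

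n = [1.960·√(2·0.375·0.625) + 1.2816·√(0.5·0.5 + 0.25·0.75)]² / 0.25² = (1.342 + 0.848)² / 0.0625 ≈ 76.7, so 77 per arm and 154 in total.

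This reproduces exactly (power 0.901). It concerns the binary primary outcome, and nothing below changes it. The article gives no dropout rate, SD, effect or correlation for the scales, so all of these are assumptions from here on.

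**2. Participants lost.** For an assumed effect of 0.5 SD with m analysed per arm, power = Φ(0.5·√(m/2) − 1.96).

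| Missing | m | Power |
|---|---|---|
| 0% | 77 | 0.873 |
| 10% | 69.3 | 0.837 |
| 20% | 61.6 | 0.792 |
| 30% | 53.9 | 0.738 |

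**3. Bias.** The simulation used 77 per arm, SD 1, no true effect and an equal correlation ρ between baseline, week 17 and week 28. Week 28 dropout was logistic in the week 17 score (slope 0, 1 or −1), with a nominal rate of 10%, 20% or 30% at an average score and 1,500 trials per setting. Sex and previous self-harm were left out. With estimate SDs near 0.19, the simulation error is about 0.19/√1500 ≈ 0.005. The table shows bias at week 28 in SD units, over nominal dropout of 10% to 30%.

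| Dropout depends on week 17 score | ρ | Complete case | Complete case plus baseline score | Using baseline and week 17 scores |
|---|---|---|---|---|
| Not at all, or alike in both arms | 0.5, 0.7 | at most 0.009 | at most 0.007 | at most 0.009 |
| In one arm only | 0.5 | 0.056 to 0.138 | 0.029 to 0.072 | at most 0.002 |
| In one arm only | 0.7 | 0.080 to 0.189 | 0.025 to 0.057 | at most 0.005 |
| Opposite directions | 0.5 | 0.120 to 0.279 | 0.055 to 0.148 | at most 0.008 |
| Opposite directions | 0.7 | 0.170 to 0.388 | 0.056 to 0.125 | at most 0.004 |

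Swapping the arms reverses the sign. For scale, at ρ = 0.5 and nominal 20% the complete-case bias is 0.102/0.175 = 0.58 standard errors for one-arm dependence and 0.209/0.178 = 1.17 for opposite directions.

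A second simulation (true difference 0.40 SD, correlation 0.6, base dropout 20% or 30%, 4,000 trials per scenario) shows the same pattern. Complete-case estimates were 0.388 with the same dependence in both arms, 0.441 to 0.457 with dependence in the DBT arm only, and 0.476 to 0.500 with opposite directions. Using week 17 scores gave 0.397 to 0.403 throughout.

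**4. What can be recovered.** With dropout unrelated to scores at nominal 30%, the SDs of the estimate in the first simulation were:

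| ρ | Complete case | Complete case plus baseline score | Using earlier scores, no adjustment for baseline differences between arms |
|---|---|---|---|
| 0.5 | 0.188 | 0.169 | 0.179 |
| 0.7 | 0.196 | 0.139 | 0.176 |

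With no missing data and no covariates the value is √(2/77) = 0.161. Earlier scores therefore recover part of the loss, and the baseline score brings the larger gain in precision. Removing the bias needs the earlier follow-up scores as well.

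**The case against.** The strongest reply is that the article nowhere says participants with missing scale scores are dropped. It promises multiple imputation in two general sentences, and a linear imputation model suits continuous scales. If many interviews are missed, the primary outcome may pass 5% as well. The scales are exploratory, and a condensed article may leave their missing-data handling to the full protocol or analysis plan.

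Much of this stands. Dropping is the default consequence of the stated model, not a stated rule, and the scope of imputation is ambiguous rather than denied. The general sentences do not resolve it: the first defers to a rule that then speaks only of the primary outcome, and the second adds no rule. The regression and its covariates are stated outright, so that part is not simply left to another document.

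A reader might infer more: that missingness does differ by arm, because "In the CAMS- intervention group the therapist has to finish the treatment when achieving three consecutive non-suicidal scores on the SSF" while DBT runs a fixed and heavier 16 weeks, and that the plan therefore overstates the benefit of DBT. The documents do not support this. Those rules govern when treatment ends, not when assessment ends. Interviews fall at the same weeks after inclusion for everyone, assessors are blinded, and both treatments are planned to be over by week 17. No dropout rate or reason is given for either arm. Arm-dependent dropout is possible, and its direction is unknown.

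It is also fair to say that a mixed model is not the only remedy. Imputation that uses the earlier scores serves equally well.

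**Conclusion.** The point holds in a limited form. As written, the scale analysis uses neither the baseline score nor the other visits, and the operative imputation rule can stay inactive while scale data are missing.

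The loss of precision does not depend on the reason for dropout. It amounts to power of 0.873 falling to 0.738 at 30% missing for an assumed 0.5 SD effect, of which a better model recovers a part.

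Bias is conditional. It is about nil if dropout works alike in both arms. Under the assumed arm-specific mechanisms it is 0.06 to 0.19 SD (one arm) or 0.12 to 0.39 SD (opposite directions), with either sign. These sizes rest on the assumed correlations, slopes and dropout rates, and on every dropout having a week 17 score.

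The primary outcome and the sample size of 154 are unaffected. Severity is minor, because the scales are exploratory.

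**What to change.** In Sample size and statistical analyses, replace the sentence on continuous outcomes by one of these:

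- **Repeated-measures likelihood model, one per scale.** Include weeks 17, 28 and 52, arm-by-visit, the stratification covariates (sex and previous self-harm) and the scale's baseline score. Entering baseline as a response keeps every randomized participant with any score in the model. Entering it as a covariate is simpler, but a participant with no follow-up score then adds nothing.
- **Multiple imputation extended to the scales.** Let each scale's own missingness trigger it, put arm, baseline and earlier follow-up scores in the imputation model, and analyse all randomized participants. Add the baseline score to the regression that follows.

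Either option assumes that missingness depends only on observed data. The cost is a few lines of text and slightly more analysis work. No new data are needed and the sample size does not change.
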